### Data analysis

Tables 2 and 3 include a summary of methods of data analysis for each variable. We have provided more details related to the statistical data analysis plan for quantitative data related to client outcomes, in addition to describing the economic data analysis and data analysis for the qualitative data related to implementation processes.

#### Client outcomes

We propose to test using two analysis sets: ITT set, considering all patients as randomized regardless of whether they received the intervention and a “per protocol” analysis set. A per protocol analysis will include all participants who received the intervention including both members of a couple assigned to the intervention group compared with all participants randomized to the control group including both members of a couple assigned to the control group.

Quantitative data analysis will include descriptive analyses with means and standard deviations calculated for the continuous variables and frequencies calculated for categorical variables. Data will be summarized in tabular or graphical form. The main between-group comparison will take place at 6 months. This point also serves as the control group’s baseline as they move into the intervention arm based on the delayed design. The comparison at 12 months then compares the effect of the intervention after 12 months of participation (original intervention group) versus 6 months of intervention (original control group).

The analysis will be blind to study group allocation and will follow ITT principle. Dropouts will not be replaced. Reporting will follow the CONSORT extension for pragmatic randomization trials [66] and non-pharmacological interventions [67]. The baseline characteristics of the practices and patients will be reported by group as mean (standard deviation) or median (first quartile, third quartile) for continuous variables, depending on the distribution, and count (percent) for categorical variables. Multiple imputations will be used to handle missing data to enable ITT analysis. The data will be analyzed using generalized estimating equations—assuming exchangeable correlation structure adjusting for baseline scores, to analyze all outcomes [68]. The results will be reported as estimate of the effect, corresponding 95 % confidence interval and associated *p* values. All *p* values will be reported to three decimal places with those less than 0.001 reported as *p* < 0.001. The criterion for statistical significance will be set a priori at alpha = 0.05 and adjusted using the Bonferroni method for multiple secondary analyses. Analyses will be performed using SAS V9.4 (Cary, NC). There will be a single final analysis at the end of the trial. Subgroup analyses will include examining differences between the following groups: men and women; age less than 80 and 80+ years; those residing alone and residing with others; or those with three or more chronic conditions.

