### Randomization and blinding

While it is recognized that there could be potential contamination between intervention and control groups by the primary care providers who will have participants in both arms, the intervention focuses on identifying a person’s health goals which a salient component to all other actions to take place as part of the intervention. Thus, without the processes in place to receive information about a person’s goals, contamination is unlikely, and so it was felt that clustering at the level of the practice was not necessary.

The randomization process will involve an automated central (allocation concealed) computerized randomization sequence, with the patient as the unit of randomization. Randomization will be stratified by participant gender and MFHT site (McMaster Family Practice or Stonechurch Family Health Centre). Couples will be accepted into the study to encourage study participation and to ensure equitable access to the intervention. Recognizing the potential influence of one member of a couple on the other, both members will be randomized into the same group. One member of the couple will be randomly selected to contribute their data to the main analysis.

Participants, caregivers, and volunteers will not be blinded; however, there will be some masking of groups: participants will not explicitly be told that they are in the initial or delayed group. Physicians and other members of the healthcare team will be not be formally blinded to allocation; however, there will be some masking as they will only know a participant is receiving the intervention once a Health TAPESTRY report is reviewed and may not recognize whether a person has been allocated to the intervention or control group. Data analysts will be blinded to the study group.

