#### Power and sample size

Assuming baseline scores of 30 on the GAS score in intervention and control groups and a standard deviation of 15 with a power of 80 % and type I error probability of 0.05, we will need to enroll 286 patients overall to detect a mean difference of 5 points on the GAS score representing improvement in the level of goals attained in the intervention group compared with control [71–73]. Previous studies in older adults have demonstrated that this difference indicates a meaningful change in effect and is achievable [71–73]. This sample size will also give sufficient power to detect a difference of 1.0 (SD, 2.5) on the self-efficacy for managing chronic disease scale [54] and a difference of 0.10 (SD, 0.3) on the EQ-5D-5L measure, both identified as meaningful differences. The study will not be powered for planned subgroup analyses, and so these will be considered exploratory. To account for a 10 % potential loss to follow-up in the study, we will aim to enroll 316 participants.

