Interventions and expertise	Experimental intervention-flexibility	TAP-reports reviewed and action plan is developed for that particular person based on their individual self-report information so action plans are all different. There is not a “one size fits all” approach to reports. No specific instructionsgiven to intake teams on process, allowed teams to develop own process and workflow for TAPESTRY; practice was allowed to be different between the two clinics. Never forced clients to use PHR to facilitate connection to healthcare team. At least one home visit by the volunteer was initiated, but no minimum or maximum follow-up visits were enforced in the trial	5
	Experimental intervention-practitioner expertise	MFHT and intake teams made up of different people, intake teams changed throughout the trial, elements of care plan carried out by various MFHT members, regardless of level of expertise	5
	Comparison intervention-flexibility	Control individuals allowed to receive any type of care from any healthcare professional at the clinic. Individuals in the control group do not receive volunteer visits, the TAP-App and are not discussed at the intake team meetings	5
	Comparison intervention-practitioner expertise	Same MFHT members are involved in the care of individuals in the intervention and control groups	5
Follow-up and outcomes	Follow-up intensity	Formal follow-up to collect research outcomes (baseline, 6 and 12 months). No formal volunteer home visit follow-up schedule of clients, no instruction for MFHT of clinic follow-up	4
	Primary trial outcome	Primary out is GAS score, which is subjective, person-centered care outcome and clinically meaningful to client	5
Compliance/adherence	Participant compliance with “prescribed” intervention	No formal strategy to encourage compliance; methods to encourage use of PHR, improve volunteer confidence in role	5
	Practitioner adherence to study protocol	Only subtle strategies to encourage intervention to move forward have left for organic process, but no formal strategy to monitor adherence or encourage adherence; researchers sat in intake team meetings early on to track development of processes, however, have withdrawn researchers have intake teams to lessen influence of initiative	4
	Analysis of primary outcome	Using intention to treat principle, intention to include all experiences in evaluation (good and bad), statistical analysis plan will work under “noise”	5

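### The per-protocol contrast drops non-recipients from the intervention arm only and changes the couple rule, so it is not a randomised comparison and cannot be read as an adherence effect

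*Protocol article*

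**What the plan says.** The Client outcomes part of the Data analysis section proposes testing in two analysis sets. The first is the "ITT set, considering all patients as randomized regardless of whether they received the intervention". The second is labelled per protocol. Its intervention side is defined by receipt: "A per protocol analysis will include all participants who received the intervention including both members of a couple assigned to the intervention group". Its control side is defined by randomisation alone: "compared with all participants randomized to the control group including both members of a couple assigned to the control group".

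The same section then states the governing principle: "The analysis will be blind to study group allocation and will follow ITT principle". The PRECIS table in the Discussion also assigns intention to treat to the primary outcome.

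Couples are randomised together. For the main analysis, the Randomization and blinding section says: "One member of the couple will be randomly selected to contribute their data to the main analysis".

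On exposure, the PRECIS table says: "At least one home visit by the volunteer was initiated, but no minimum or maximum follow-up visits were enforced in the trial". The Control section says that controls get no volunteer visits and are not discussed at intake meetings. They may take up the intervention after 6 months.

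**The concern.** Selection on receipt is applied to one arm. People who would not receive the intervention are taken out of the intervention arm, while people of the same kind remain among the controls. The two groups then differ by more than allocation, and the difference in their means estimates the intervention effect plus a selection term. The article describes no adjustment for selection into receipt.

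The couple rule changes in the same step. If the per-protocol estimate differs from the ITT estimate, a reader will take the gap as the effect of actually receiving the programme. It could come from selection, or from letting each couple contribute two people instead of one. The design offers no way to separate these.

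What is at stake is the interpretation of a second test of effectiveness, reported beside ITT and not labelled exploratory in the article.

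**Working it through.** **Inputs.** From Power and sample size: SD 15, target difference 5 GAS points, 80% power, "type I error probability of 0.05", 286 participants before loss to follow-up. Assumed because not stated: 1:1 allocation, a two-sided test, and all quantities describing non-receipt.

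**The plan's own figure.** Per arm, n = 2 × (1.960 + 0.842)² × 15²/5² = 141.3, so 142 per arm and 284 in total. The t-test version gives 142.25, so 143 per arm and 286 in total, as stated. Also 284/0.9 = 315.6, which rounds up to the stated 316. The sample size is not in dispute, and 143 per arm is used below.

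**Bias with no true effect.** Let q be the share of the intervention arm excluded as non-recipients and g the mean GAS deficit of would-be non-recipients, the same in both arms by randomisation. If the overall mean is m, recipients average m + q × g, while the full control arm averages m. The per-protocol contrast therefore has bias q × g. It is zero if g = 0 and negative if g is negative.

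To tie g to a correlation, suppose receipt depends on a normally distributed propensity that has correlation r with the GAS score. Then bias = r × 15 × φ(z)/(1 − q), where z is the normal quantile at q and φ the normal density.

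| q | r | φ(z) | Bias (points) | Implied g = bias/q | Simulated false-positive rate |
|---|---|---|---|---|---|
| 5% | 0.2 | 0.103 | 0.2 × 15 × 0.103/0.95 = 0.33 | 6.5 | about 5% |
| 10% | 0.2 | 0.175 | 0.2 × 15 × 0.175/0.90 = 0.58 | 5.8 | about 6% |
| 20% | 0.3 | 0.280 | 0.3 × 15 × 0.280/0.80 = 1.58 | 7.9 | about 13% |
| 30% | 0.5 | 0.348 | 0.5 × 15 × 0.348/0.70 = 3.73 | 12.4 | about 49% |

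The rates are two-sided at 0.05, from 20,000 simulated trials per row with independent participants and no covariates. ITT on the same data rejects in about 5%. With r negative, each bias changes sign and keeps its size.

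**Cross-check by setting q and g directly.** At q = 20% and g = 10, bias = 0.20 × 10 = 2.0 points, with a simulated false-positive rate of 19.2% (ITT on the same data: 4.8%). At q = 10% and g = 5, bias = 0.5 points and the rate is 5.8%.

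**The alternative estimator.** Controls have no visits before 6 months, so the complier effect is the ITT difference divided by the proportion visited, 1 − q. With no true effect it is centred on zero (simulated means between −0.05 and 0.05). Its standard error is approximately that of ITT divided by 1 − q. The ITT standard error is 15 × √(2/143) = 1.77.

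- At q = 5% this gives 1.77/0.95 = 1.87, against 1.79 for the per-protocol contrast: about 4% wider.
- At q = 20% it gives 1.77/0.80 = 2.22, against 1.86: about 19% wider.

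The per-protocol standard errors are √(v/(143(1 − q)) + 225/143) with v = 225 − q(1 − q)g².

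**The case against.** The strongest reply is that ITT governs. The analysis principle, the PRECIS entry for the primary outcome and the one-member couple rule for the main analysis all point to it. A reader might infer that the trial's main result is compromised; the article does not support that. In a delayed-start design the controls also have nothing to receive before 6 months, so a receipt rule can only act on one arm. That explains why the rule is one-sided but does not remove the bias.

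A reader might also infer that the bias favours the intervention, because frailer or less engaged people would miss visits. Nothing in the article shows this. GAS is scored against each person's own goals, the PRECIS table describes the sample as quite healthy, and well people might decline visits as unnecessary. The sign stays open.

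A false-positive rate near one half is not a fair headline. It needs 30% non-receipt and a 12.4-point deficit among non-recipients, which is 0.83 SD (12.4/15). The article records that at least one visit was initiated, so low non-receipt is plausible, and at 5% the effect is small.

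Nor does the article leave couples without any method. It specifies GEE with an exchangeable correlation for all outcomes. The cluster unit is not named, but that model could accommodate couples, and keeping both members does not itself break randomisation because they are allocated together.

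Adjustment for baseline scores, gender and site might absorb part of the selection. For GAS this is uncertain, because Table 2 lists goal attainment at 6 and 12 months only.

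What remains is the one-sided exclusion combined with a changed couple rule, which nothing elsewhere in the article corrects.

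**Conclusion.** The point holds for the per-protocol comparison and not for the ITT primary result. As defined, the contrast is non-randomised and is biased whenever receipt is related to outcome. Because the couple rule changes too, its distance from ITT is not an adherence effect.

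The size and sign cannot be derived from the article. Under the assumptions shown, the spurious difference runs from about 0.3 to 3.7 points against a 5-point target. It is zero if receipt is unrelated to outcome and negative if the relation is negative. These figures assume 143 independent participants per arm and no covariate adjustment; they are an illustration, not a forecast.

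**What to change.** Replace the one-sided per-protocol contrast at 6 months with a complier average causal effect. Use randomised arm as the instrument for receipt of at least one volunteer visit, adjust for gender and site, and apply the same couple rule as the ITT set. If both members of couples are kept, use household-clustered standard errors. Confine this to 6 months, because controls may take up the intervention afterwards.

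If the per-protocol contrast is kept, define receipt, label the contrast exploratory and non-randomised, and align its couple rule with ITT.

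The cost is wording. Volunteer visits already leave electronic TAP-App records and reports, so no new data are needed. The interval is wider than the per-protocol one. The estimate also assumes that assignment without a visit has no effect on outcome. Because the intervention includes a personal health record and team contact as well as visits, that assumption should be stated and defended.

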### Overall objective, research questions, and hypothesis

We aim to evaluate the implementation and effectiveness of the Health TAPESTRY approach in older adults. The primary research question is, what is the effectiveness of the Health TAPESTRY approach on the identification and attainment of a person’s health goals in older adult participants compared to people not receiving the Health TAPESTRY approach? Our hypothesis is that better integration of the health and social care systems into a person’s life will allow a person to better attain their health goals. Four secondary research questions will also be asked with respect to several participant outcomes, cost-effectiveness, sub-analyses, and intervention duration (see Additional file 1 for a complete list of secondary research questions). An additional set of questions will be asked related to the processes of implementation of each component of the Health TAPESTRY approach (see Additional file 1).

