## Methods/design

### Design

This is an unblinded delayed intervention pragmatic RCT. Participants in the control group will receive the intervention at 6 months, and both groups will continue to be part of the study until the 12-month mark (Fig. 1). The main analysis will be group comparisons at 6 months. Both groups will be also assessed at 12 months. Ethics approval was granted from the Hamilton Integrated Research Ethics Board (8 December 2014). The trial has been reregistered with Clinical Trials.gov NCT02283723. We used the SPIRIT guidelines to guide reporting of our trial protocol [47].

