**Fig. 2 Fig2:**
[figure not shown]
Health TAPESTRY process. Volunteers visit clients in their home and use the Health TAP-App to collect information. This information is summarized on a Health TAPESTRY report and is uploaded into the person’s electronic medical record to be shared with the intake team at the clinic. Reports are viewed and an action plan is developed which can include community organizations and resources, volunteer follow-up visit, and follow-up in any nature by healthcare team members and the client using their personal health record. The Health TAPESTRY process continues in an iterative fashion until the participant is discharged from the program

Each clinic will decide which healthcare team members should be included in the intake team and define a process that works best within their workflow. The clinic intake teams will review the reports and connect with the appropriate interprofessional healthcare team across the MFHT making sure to include the most responsible family physician. Collectively, a care plan is generated to facilitate how the team, community agencies, and the volunteers can address the client’s goals and health issues. The intervention treatment period will be 6 months.

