### Control

The control group will receive the usual care. These individuals will not have volunteer visits or be discussed at an intake meeting. They may or may not have had a previous PHR account. At the conclusion of the 6-month trial, the control group will have the option of receiving the intervention.

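### The 12-month comparison is worded as longer versus shorter intervention, but under ITT it compares early with delayed offer and does not by itself support a conclusion about duration

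*Protocol article*

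**What the plan says.** All references are to the protocol article.

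- **Data analysis, Client outcomes:** the 12-month comparison "compares the effect of the intervention after 12 months of participation (original intervention group) versus 6 months of intervention (original control group"). The main between-group comparison is at 6 months. Of that visit the section says "This point also serves as the control group’s baseline as they move into the intervention arm".
- **Intervention, closing sentence:** "The intervention treatment period will be 6 months".
- **Fig. 2 legend:** the process "continues in an iterative fashion until the participant is discharged from the program". No length is attached.
- **Design:** "Participants in the control group will receive the intervention at 6 months".
- **Control:** after 6 months "the control group will have the option of receiving the intervention".
- **Overall objective, research questions, and hypothesis:** the four secondary questions cover "several participant outcomes, cost-effectiveness, sub-analyses, and intervention duration". Their full text is in Additional file 1, which is not shown.
- **Analysis principle:** Client outcomes defines an ITT set of all patients as randomized, whether or not they received the intervention, and adjusts all outcomes for baseline scores.

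**The concern.** The 12-month sentence sets 12 months in one arm against 6 months in the other, and the reader is led to see a dose of time. For that reading to hold, the original intervention arm would have to be exposed through month 12 and the controls would have to take up the intervention. The article states neither consistently. If treatment lasts 6 months, the original intervention arm is seen at month 12 six months after its period ended, and the controls are seen at the end of theirs. If uptake is optional, the control arm under ITT is a mixture of treated and untreated people.

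Duration is a named secondary topic. A 12-month difference, or its absence, could be reported as evidence on how long the programme should run when it reflects fading of effect or incomplete uptake.

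**Working it through.** **1. The statements side by side.**

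| Question | One statement | Another statement |
|---|---|---|
| Exposure of the original intervention arm by month 12 | Fixed 6-month period (Intervention) | Until discharge, length open (Fig. 2 legend); 12 months of participation (Client outcomes) |
| Exposure of controls from month 6 to 12 | Will receive it (Design); 6 months of intervention (Client outcomes) | Optional (Control) |

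Under the 6-month period, neither arm has more than 6 months of treatment by month 12. Under the legend, exposure varies by person, and Table 4 adds that no minimum or maximum number of follow-up visits was enforced. Neither gives a fixed 12 versus 6 months. The Client outcomes sentence also uses participation for one arm and intervention for the other, which blurs follow-up time with exposure.

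**2. The planning figures reproduce.** Inputs from Power and sample size: difference 5, SD 15, power 80%, alpha 0.05 (taken as two-sided).

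- Normal approximation: n per arm = 2 × (1.960 + 0.842)² × 15² / 5² = 141.3, so 142 per arm and 284 in total.
- The t-test version gives 142.2, so 143 per arm and 286 in total, which is the stated figure.
- With 143 per arm, the standard error of a difference is 15 × √(2/143) = 1.77, and power for 5 points is 80.5%.

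**3. What the 12-month contrast estimates.** Let r be the share of the 5-point effect still present at month 12 in the original intervention arm, u the share of controls who take up the intervention (with the same 5-point effect in those who do), and g any true gain from longer exposure. Then

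expected 12-month difference = 5 × (r − u) + g.

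One observed difference cannot separate three unknowns. An expected +1.5, for example, arises from r = 1, u = 0.7, g = 0, and equally from r = 1, u = 1, g = 1.5.

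**4. Illustration with no duration effect (g = 0).** The values of r and u are assumptions; the documents give neither.

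| r | u | Expected difference |
|---|---|---|
| 1 | 1 | 5 × 0 = 0 |
| 1 | 0.7 | 5 × 0.3 = +1.5 |
| 0.5 | 1 | 5 × (−0.5) = −2.5 |
| 0.5 | 0.7 | 5 × (−0.2) = −1.0 |

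**5. Chance of a significant result from uptake alone** (r = 1, g = 0, 143 per arm, SD 15, two-sided 0.05 without the Bonferroni adjustment).

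| Control uptake | Expected difference | Chance of p < 0.05 |
|---|---|---|
| 100% | 0 | 5% |
| 80% | 1 | 9% |
| 60% | 2 | 20% |
| 40% | 3 | 39% |

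Conversely, if r = u and there is a true gain from longer exposure, power is about 10% for a gain of 1.25 points and 29% for 2.5 points.

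**The case against.** The best defence has four parts.

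- **The sentence does not claim 12 months of treatment.** It says participation for the intervention arm, which fits both groups staying in the study to month 12. This is fair: the fault is the exposure contrast that the wording invites. The conflict with the 6-month period and with optional uptake remains.
- **The until-discharge wording may govern.** Some participants could then be exposed beyond 6 months, and with full uptake the contrast would come nearer to one of duration. So it would be too strong to say that the comparison can never bear on duration; that depends on the 6-month sentence governing. Even under the legend, exposure is variable and uptake still matters.
- **Optional uptake is no flaw under ITT.** Correct. The comparison of early with delayed offer is a valid randomized comparison. Only the duration interpretation falls.
- **The duration question is not tied to this contrast.** Its wording is in Additional file 1, and Client outcomes does not link the two. The point therefore rests on what the 12-month contrast can support, not on a claim that the trial will use it to answer that question.

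A reader might go further and infer that the control baseline is replaced at month 6, so that 12-month GAS is rated from T0 in one arm and T6 in the other. The documents do not show this. Month 6 is said to serve also as the controls' baseline, which suits their own before-after change. The article does not say which baseline enters the 12-month model. GAS procedures are left to Additional file 5, and the Discussion says that both groups use the same process of reporting change from baseline.

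**Conclusion.** The point holds as a matter of interpretation and inconsistent wording in a secondary comparison. As described, the 12-month between-arm contrast estimates the effect of early versus delayed offer. It combines persistence, uptake and time since start, and by itself does not support a statement about longer versus shorter intervention.

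The differences of −2.5 to +3 GAS points shown above are illustrative only. They rest on assumed persistence and uptake, on an equal effect in delayed takers, and on a duration effect set to zero. They show that the contrast can move in either direction without any effect of duration; they do not predict the trial's result. The main comparison at 6 months, and the sample size that supports it, are untouched.

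**What to change.** 1. In Data analysis, Client outcomes, describe the 12-month between-arm comparison as early versus delayed offer of the intervention under ITT, and remove the reading as 12 versus 6 months.
2. For outcomes that Table 2 lists at T0, state that the 12-month between-arm model adjusts for the T0 value in both arms.
3. Report the T6 to T12 change within each arm as descriptive: persistence in the original intervention arm, and before-after change in the controls.
4. Reconcile the treatment-period sentence in Intervention with the Fig. 2 legend and with Client outcomes, and reconcile Design with Control on whether controls receive the intervention or may choose it. Which statements are right is for the investigators to settle.

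The cost is wording. No data collection or sample size changes; the trial gives up a duration conclusion that this contrast does not support.

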#### Primary outcome

The primary outcome is the mean difference in the goal attainment scale (GAS) score at 6 months over baseline in the intervention arm, compared with the control group [52]. Participants will identify health goals, indicators, and outcomes through structured, prompted discussion. Each participant will rate their progress towards achievement of their goal using a set of five expected outcome levels for each indicator related to that of health goal. Outcome levels identified will be as descriptive, objective, and observable as possible and phrased as relative versus absolute improvements [53]. At 6 months, a GAS score will be calculated for each participant according to conventional methods [52] and used as the primary outcome. The proportion of participants’ self-reporting maintenance or improvement in their top priority goal area will be used as a secondary outcome. Further details about the process for gathering data to create the GAS are provided in Additional file 5.

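### Secondary outcomes are adjusted by single-step Bonferroni; Holm's procedure gives the same familywise control with at least as much power and costs one word

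*Protocol article*

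**What the plan says.** Under Data analysis, Client outcomes, the protocol article gives a reporting rule and a decision rule. The reporting rule is "The results will be reported as estimate of the effect, corresponding 95 % confidence interval", followed by p values; it sets no other level for secondary outcomes. The decision rule is "The criterion for statistical significance will be set a priori at alpha = 0.05 and adjusted using the Bonferroni method for multiple secondary analyses".

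The number of tests in the adjusted family is not stated. Table 2 and the Secondary outcomes section list ten scales and items: self-efficacy, EQ-5D-5L, optimal aging, social support, access, comprehensiveness, empowerment, patient-centeredness, caregiver strain and satisfaction. Hospital and emergency use comes on top, in three categories. The Primary outcome section adds the proportion with "maintenance or improvement in their top priority goal area will be used as a secondary outcome".

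Power and sample size gives planned effects for two secondary outcomes only: "a difference of 1.0 (SD, 2.5) on the self-efficacy for managing chronic disease scale" and "a difference of 0.10 (SD, 0.3) on the EQ-5D-5L measure".

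**The concern.** Single-step Bonferroni holds every secondary p value to 0.05/m, where m is the number of tests. Holm holds only the smallest p value to that level and relaxes the threshold for each later one, provided all the earlier ones were rejected. Both bound the familywise error at 0.05 under any dependence between the tests. Bonferroni therefore leaves some of the allowed error unused whenever at least one effect is real.

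Table 2 predicts a favourable difference on every listed outcome. The more of those predictions are true, the more Bonferroni loses against Holm. What is at stake is power on secondary outcomes, for a change of wording that touches neither sample size nor conduct.

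A lesser matter is presentation. A secondary result can fail the adjusted test while its printed 95% interval excludes no effect, and the article does not label those intervals as unadjusted.

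**Working it through.** **The plan's own sample size.** The inputs are "a standard deviation of 15 with a power of 80 % and type I error probability of 0.05" and "we will need to enroll 286 patients overall to detect a mean difference of 5 points on the GAS score". Assume a two-sided test and 1:1 allocation, neither of which is stated.

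- Normal approximation: n per arm = 2 × (1.960 + 0.842)² × 15²/5² = 141.3, so 142 per arm and 284 in total.
- t-test version: 142.2, so 143 per arm and 286 in total. The stated figure reproduces.
- With 10% loss, 284/0.9 = 315.6, which rounds up to the stated 316; 286/0.9 = 317.8. The difference has no bearing here. The check below uses 143 analysed per arm.

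**Number of tests.** The ten scales and items plus the top-goal proportion make 11. Hospital and emergency use adds 1 (a single row), 2 (two outcomes) or 6 (two outcomes in three categories), so m = 12, 13 or 17. This is a count of 6-month outcomes, not a stated figure. Adding 12-month or subgroup tests would raise it.

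**Effect size.** EQ-5D-5L: 0.10/0.3 = 0.33. Self-efficacy: 1.0/2.5 = 0.40. The check uses 0.33 for every real effect. The expected test statistic is 0.333 × √(143/2) = 2.82.

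**Bonferroni power per effect**, Φ(2.82 − z), where z is the two-sided critical value at 0.05/m:

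- m = 11: level 0.0045, z = 2.838, power 49.2%
- m = 12: level 0.0042, z = 2.865, power 48.1%
- m = 13: level 0.0038, z = 2.891, power 47.1%
- m = 17: level 0.0029, z = 2.974, power 43.8%

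**Holm.** Order the p values and compare the j-th smallest with 0.05/(m − j + 1), stopping at the first failure. At m = 13 the first three thresholds are 0.05/13 = 0.0038, 0.05/12 = 0.0042 and 0.05/11 = 0.0045. Suppose the three smallest p values are 0.001, 0.002 and 0.0041. Holm rejects all three. Bonferroni rejects two.

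**Gain in power per true effect.** Simulation with 200,000 replicates, normal test statistics with common correlation 0.3, and all real effects at 0.33. Entries are Holm minus Bonferroni in percentage points; Monte Carlo error is below 0.1.

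| m | 2 real | 4 real | all real |
|---|---|---|---|
| 11 | 0.6 | 2.0 | 11.2 |
| 12 | 0.6 | 1.8 | 11.1 |
| 13 | 0.5 | 1.6 | 11.0 |
| 17 | 0.35 | 1.1 | 10.4 |

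No replicate had Bonferroni rejecting where Holm did not. At m = 11 with four real effects, the chance of any false rejection was 3.0% for Bonferroni and 3.7% for Holm, both under 5%. If nothing is real, the two coincide, because the first step is the same.

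**Sensitivity to effect size.** At m = 11 with every real effect at 0.40, power goes from 71% to 73% with four real effects and from 71% to 83% with all real.

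**Interval against test.** A 95% interval excludes no effect when p is below 0.05. The Bonferroni test needs p below 0.0029 (m = 17) to 0.0045 (m = 11). Results between those values and 0.05 show the mismatch. Intervals matching Bonferroni would have level 1 − 0.05/m, that is 99.55% to 99.71%, and be 2.838/1.960 = 1.45 to 2.974/1.960 = 1.52 times as wide as 95% intervals.

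**The case against.** Bonferroni controls the familywise error, so nothing in the plan is stated wrongly, and preferring Holm is a matter of efficiency. That stands. It is also fair that the gain is negligible if few effects are real, and that only two secondary outcomes have a planned effect, so the 10 to 11 point figure belongs to a favourable scenario. Nor is power given up for nothing: Bonferroni has simple simultaneous intervals at level 1 − 0.05/m that agree exactly with its tests, and Holm does not. A team that values that agreement above power could reasonably keep Bonferroni.

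Two stronger readings are tempting. A reader might infer that 95% intervals beside a Bonferroni threshold are contradictory rules, and might add that with 11 to 17 independent null outcomes the chance of at least one interval excluding no effect is 1 − 0.95^11 = 43% to 1 − 0.95^17 = 58%. The article does not support this. It ties significance to the adjusted alpha and nowhere says that significance is read from an interval. Conventional intervals beside an adjusted threshold are ordinary practice, and the 43% to 58% is the error rate of a rule the plan does not adopt. A reader might also infer that confirmatory tests are being weakened; the article does not call its secondary outcomes confirmatory.

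What survives is that Holm is never less powerful at the same error bound, that the article names the weaker procedure, and that a label on the intervals would help the reader.

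**Conclusion.** The point holds as a low-cost improvement. Bonferroni as stated is valid but dominated by Holm in power. The size depends on how many effects are real: about 0.5 points per true effect for two, 1 to 2 for four, and 10 to 11 for all. These figures assume 11 to 17 tests, 143 analysed per arm, a standardised effect of 0.33 for every real effect, and correlation 0.3. The dominance itself needs none of these assumptions. The interval matter is a reporting clarification only. The primary goal attainment comparison keeps its level, interval and power.

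**What to change.** In Data analysis, Client outcomes, name Holm instead of Bonferroni for the secondary tests and state that secondary significance follows the Holm-adjusted p value. Add one sentence saying that the 95% intervals for secondary outcomes are unadjusted for multiplicity and do not decide significance.

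The cost is two sentences, with no change to data, conduct or sample size. If intervals at level 1 − 0.05/m are also shown, say that they are conservative relative to the Holm tests: Holm may occasionally reject where such an interval just includes no effect.
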